Following screening, 60 patients presenting MRSE (assessed by a standardized questionnaire; see **Appendix 3, questionnaire 3**) under statin monotherapy (any statin, any dosage) as well as 30 patients without MRSE under statin monotherapy (paired for statin and dosage with the MRSE cohort) will be evaluated. Muscle strength and fatigability will be tested by standardized procedures before and after two months of stopping statin monotherapy. Briefly, strength of the extensors and flexors muscles of the dominant leg will be quantified with a Biodex isokinetic dynamometer available in our research centre. Forces will be tested during 3 reps at 60 and 180 deg/sec and endurance during a 15 reps test at 180 deg/sec. These tests will be preceded by a 5 reps warm-up at 60 deg/sec including one movement at maximal voluntary contraction [46]. Each maximal concentric contraction will be performed in the first 90 degrees of the knee range of motion. Patients will sit in an upright position and mechanical axis and resistance pads will be aligned according to the manufacturer's guidelines. The results will be reported in Newton-meters (Nm). Peak torque, rate of torque development and total work values will be obtained following these isometric and isokinetic measurements. These groups of muscles were selected because muscle weakness or myalgias with statins are most frequently localized in lower limbs. Handgrip strength of the dominant hand will also be tested in a static mode with a Jamar dynamometer (best of 3 repetitions). These testing procedures are well standardized, easy to perform and very reproducible, and are routinely used in the department of physical therapy at our centre. Test-retest variability for the Biodex measurements is shown to be within  $\pm 15\%$  [46], which our personal experience confirms. The primary efficacy parameter will be the percent change for these measurements from baseline to end of each phase of the study.

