**Trial design**

This study will use an outpatient, randomized, double-blind (participants, research nurse, coordinator, investigators, interviewers, statisticians, treating physicians), prospective trial design with stratification on MRSE status, plasma 25(OH)D status, age and sex, with repeated measures at 4 weeks post-randomization and at up to 8 weeks post-statin reintroduction. This is diagrammed in Figure 1. Participants (from Objective #1) will first be divided into 2 groups according to their MRSE status: statin taking with MRSE and statin taking without MRSE. Participants in each group will then be randomly assigned to either the experimental (vitamin D) or the control (placebo) arm. The placebo will as closely as possible match the color, taste and consistency to the vitamin D administered in the experimental group.

The research coordinator and other members of the research team will be responsible for recruitment, testing, data collection and follow-up. Allocation of participants to treatment arms and statin, vitamin D and placebo supply and distribution will be under the responsibility of the Department of Pharmacy of the CHUL (see budget supporting document).

Vitamin D status will not be used to select subjects for initial (Objective #1) enrolment in the study, but will be used to stratify subjects in the RCT. Subject vitamin D status will be defined using cut-offs discussed in a recent Statistics Canada Health Report [45].

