### Research Proposal

impact of stopping statin monotherapy and the rechallenge of statin monotherapy under vitamin D repletion. As described in objective #1, and for both groups, muscle strength and fatigability tests and venous punctures (particularly for 25-OH vitamin D level assessments) will be obtained immediately prior to statin reintroduction (after one month of vitamin D or placebo). These and muscle biopsies will also be taken at the end of the statin-reintroduction period (within 1 week of the maximum 2 months trial length or from when patients cease statin use due to reappearance of important MRSE).

Muscle biopsies of the *vastus lateralis* will be obtained for 30 of these patients: 10 presenting MRSE and receiving vitamin D, 10 presenting MRSE and not receiving vitamin D, 5 without MRSE and receiving vitamin D, and 5 without MRSE and not receiving vitamin D. These will be the same patients that had biopsies in objective #1, allowing us to evaluate changes to skeletal muscle tissue over time. Our laboratory has extensive experience in multiple biopsies from the same patient over time, and we have published numerous papers using this approach (e.g., [49, 53-57]).

In addition to the testing and questionnaires outlined in Figure 1, phone interviews will be performed every 2 weeks during the RCT to assess adverse events. An adverse event is any untoward medical occurrence in a study subject that is temporally associated with the use of a medicinal product, regardless of its potential relationship to the medicinal product. An adverse event, therefore, can be any unfavorable or unintended sign, symptom or disease (new or exacerbated), whether or not related to the study drug. The severity of an adverse event will be scored according to the following scale:

Mild: Awareness of sign or symptom, but easily tolerated

Moderate: Discomfort enough to cause interference with usual activity

Severe: Incapacitating with inability to perform usual activities

Participants will be provided with the adverse event guide presented in **Appendix 3** to help classify the nature and intensity of adverse events during phone interviews and in questionnaires.

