## **5.0 STATISTICAL ANALYSES**

Although there are no published data on the loss of muscle force in humans following statin treatment, experiments using men with coronary artery disease showed that  $n = 10$  to  $20$  is sufficient to distinguish differences between groups [58]. Based on the high accuracy of the Biodex apparatus and our preliminary data, we calculate that a total of 60 MRSE suffering patients will be sufficient to demonstrate effects on muscle function by statin withdrawal or vitamin D supplementation (30 per group, one with vitamin D, the other with placebo - see APPENDIX 3 for Power Calculations). These sample sizes are similar to those producing data showing reversible myositis-myalgia in statin-treated low serum 25(OH)D patients receiving vitamin D repletion [43, 44]. For biopsies, the number of subjects in each study group was determined based on our previous work (*e.g.*, [49]), biopsy feasibility and the availability of patients from our clinic [59]. From the patient case reports documented with some of these MRSE and considering the analytical precision of the methods proposed, we are confident that we will show statistically significant differences between MRSE suffering and not suffering patients [13].

Statistical analyses will test the comparison of subgroups (with/without symptoms and with/without vitamin D repletion) on the percent change from baseline (end – baseline) of specific measurements. Changes from baseline (end – baseline) of all clinical muscle symptoms will be also analyzed. Normal distribution of fasting marker levels will be examined and, if necessary, they will be normalized by transformation prior to statistical analyses in order to reduce the skewness of their distribution. One-way ANOVA will be used to compare means of continuous variables. Differences in proportions (*e.g.* proportion of patients having increments in one or more specific markers) will be compared using either the Chi-square test, or the Fisher's exact test when appropriate. Statistical analyses will be performed using SAS (SAS Institute Inc.) and/or JMP (SAS Institute Inc.) software. All tests will be two-tailed and considered statistically significant when alpha level  $< 0.05$ .

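### Objective #2 muscle function is fixed as one-way ANOVA on percent change: valid, but inefficient and without a defined baseline, where a baseline-adjusted log-scale ANCOVA on data already collected would do better

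*Protocol*

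**What the plan says.** The section on functional assessment under Objective #1 sets the primary quantity for the strength and endurance tests: "The primary efficacy parameter will be the percent change for these measurements from baseline to end of each phase of the study". Section 5.0 carries this into the analysis as a "comparison of subgroups (with/without symptoms and with/without vitamin D repletion) on the percent change from baseline", and adds that "One-way ANOVA will be used to compare means of continuous variables". The same section glosses percent change as end minus baseline, which is an absolute difference. Its provision for transforming skewed data names only fasting marker levels, so it does not reach torque or work.

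The Trial design section of Objective #2 describes randomisation with "stratification on MRSE status, plasma 25(OH)D status, age and sex", and "repeated measures at 4 weeks post-randomization and at up to 8 weeks post-statin reintroduction". No section supplied names a baseline covariate, an adjusted or stratified model, or a repeated-measures model for muscle function. The Subjects section of Objective #1 says that 25(OH)D will be examined after the study as a contributor to statin tolerance, without a model.

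**The concern.** Design and analysis do not match. The trial stratifies on four factors and measures strength off statin before study capsules start, but the stated comparison uses neither as a covariate. Dividing by a baseline that carries measurement error is not the same as adjusting for it. The ratio passes the baseline error on to the outcome in full, whereas a regression slope discounts it.

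The scale is also awkward. Percent change is right-skewed and asymmetric, yet it is used for both withdrawal and rechallenge. And "baseline" has three candidates: the entry test on statin, the test after two months off statin, and the test after one month of capsules. The third is post-randomisation. If it were taken as the baseline, any strength gained on vitamin D in that month would be subtracted from the treatment effect.

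At stake is power on the main objective measure, in a trial with little to spare, and a clear meaning for the estimate.

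**Working it through.** **The plan's own figure.** Section 5.0 gives 60 MRSE patients, 30 per arm. The target power and design effect sit in an appendix that was not supplied, so 60 cannot be reproduced and is not disputed here.

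**Margin at 30 per arm.** The Preliminary data section (9 patients, withdrawal effect) gives extensor strength 22 ± 43% and flexor strength 17 ± 28%. Assume, generously, that the full withdrawal effect is the between-arm difference, with two-sided alpha 0.05 as in 5.0:

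- Extensor: SE = 43 × √(2/30) = 11.1; 22/11.1 = 1.98; power = Φ(1.98 − 1.96) = 51%.
- Flexor: SE = 28 × √(2/30) = 7.23; 17/7.23 = 2.35; power = Φ(2.35 − 1.96) = 65%.

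**Asymmetry.** 1 − 1/1.22 = 18.0%, so a 22% gain is undone by an 18% loss. In simulation (lognormal torque, CV 0.25–0.45, baseline to follow-up correlation 0.5–0.9), the placebo mean percent change with no true mean change was +0.6 to +9.7%. This bias is the same in both arms and cancels in the randomised contrast. Type I error of the percent-change ANOVA was 5.0%.

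**Why the gain varies.** Assume within-sex log-SD 0.25, a sex gap of 0.4 on the log scale and equal numbers of each sex. The true between-patient variance is 0.25² + 0.2² = 0.1025. Compare two explanations of the same spread in log change:

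- *All measurement error*, 0.26 per test. Variance of the log change = 2 × 0.26² = 0.135. Correlation = 0.1025/(0.1025 + 0.0676) = 0.60. ANCOVA variance relative to the change score = (1 + 0.60)/2 = 0.80, a 20% reduction.
- *Error 0.10 per test, the rest differing response.* Response variance = 0.1352 − 2 × 0.01 = 0.115. ANCOVA residual variance = (0.1025 + 0.01 + 0.1152) − 0.1025²/0.1125 = 0.134. Relative to 0.135 this is a reduction of under 1%.

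The protocol states Biodex test-retest variability within ±15%. Read as an SD per test, pure error would give a change SD of about 0.15 × √2 = 21%, below both preliminary strength SDs (28% and 43%). On the protocol's own figure, then, much of the spread would not be test error. Nine patients cannot settle this.

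**Simulated power**, 30 v 30, true ratio 0.82 (the mirror of +22%), with the assumptions above:

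| Source of spread | Percent-change SD | Percent-change ANOVA | Log-ANCOVA |
|---|---|---|---|
| All measurement error (20–26% per test) | about 40% | 51% | 66% |
| All measurement error | about 30% | 73% | 84% |
| Mostly patient response, test error 10% | about 40% | 50% | 52% |
| Mostly patient response, test error 10% | about 30% | 73% | 75% |
| Test error 15%, no varying response | smaller | 94–95% | 97% |

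Repeat runs of the all-error case gave gains between 8 and 15 points. With test error of 10–15% and the rest as response, the gain was about 0–4 points. Adding sex to the log-ANCOVA contributed only 1–3 points in the all-error case and none in the response case. Most of the gain comes from the baseline value and the log scale.

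**Why logs.** In the CV and correlation simulation (20% multiplicative effect), raw-scale ANCOVA with sex was slightly worse than percent change at CV 0.45 and correlation 0.9 (92% v 95%), while log-ANCOVA with sex gave 96%. At CV 0.35 and correlation 0.5, percent change gave 51% and log-ANCOVA with sex 63%.

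**The case against.** The strongest reply is that an unadjusted comparison under stratified randomisation is valid, at worst conservative, and that covariates are often left to a SAP. The first part stands. The second has less force here, because the protocol does not leave the method open: it names the quantity and the test.

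Several stronger readings are tempting and are not supported.

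- *All four stratification factors are ignored.* MRSE status defines the subgroups compared, and 25(OH)D has a planned, if vague, role for tolerance. Only age and sex are wholly absent.
- *Every continuous outcome becomes percent change.* Section 5.0 analyses muscle symptoms as plain changes from baseline.
- *Leaving out the strata makes the standard errors badly too large.* Percent change already removes the sex difference in level. Adding sex to the percent-change analysis moved simulated power from 53.5% to 53.4%.
- *The scale creates false positives.* Both arms share the scale, and type I error stays near 5%. The 22%/18% asymmetry matters only when phases with different denominators are compared.
- *The 4-week test is the baseline.* No section says so, and Trial design lists it among the repeated measures. What remains is that baseline is not defined for each phase.
- *Adjustment is worth 20–37% more patients.* That holds only if all the preliminary spread is measurement error, which sits poorly with the ±15% stated.

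**Conclusion.** The point holds as a matter of efficiency and clarity, not validity. The protocol fixes an analysis of muscle function that uses the pre-randomisation value only as a denominator, adjusts for none of the factors it stratifies on, applies a skewed scale that its transformation clause does not cover, and leaves the baseline undefined by phase.

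The power gain from log-scale ANCOVA lies between about 0–4 points and about 10–15 points. This assumes 30 v 30, a true ratio of 0.82, a percent-change SD of 30–40%, within-sex log-SD 0.25 and a log sex gap of 0.4. Where the truth falls depends on how much of the spread is test error, which the documents do not settle. Log-ANCOVA was not materially worse in any setting tried, so the change should be made even if the gain is small.

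**What to change.** In section 5.0, for muscle function in Objective #2, replace percent change and one-way ANOVA with ANCOVA of log torque (or log work) at the end of statin reintroduction. Terms: treatment, the log value at the off-statin test before randomisation, MRSE status, 25(OH)D status, age and sex. MRSE status drops out of an analysis confined to MRSE patients. Report the back-transformed treatment ratio with a 95% confidence interval.

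Define the baseline for each phase, and state that the 4-week post-randomisation test is an outcome and never the baseline. Remove the gloss that equates percent change with end minus baseline.

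Optional: a Mantel-Haenszel or adjusted logistic analysis for proportions, and log ratios for the Objective #1 withdrawal change.

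The cost is wording in the statistical section. The off-statin test and all four factors are already collected, so no new data or visits are needed.

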**Functional assessment and blood samples**

A case-control approach will be used to compare patients under statin treatment with and without MRSE. After initial testing while under statin treatment, statin treatment will be stopped for 2 months followed by retesting. Recent studies have shown that most statin MRSE as well as structural muscle damage appearance/disappearance occurs within a two month period of statin introduction/withdrawal [1, 13]. A control group of 10 statin-naïve patients will also be included for test-retest variability assessment of all parameters.

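### Patients without MRSE are paired to the MRSE cohort on statin and dosage, but the named tests ignore the pairing, which may cost precision in that Objective #1 comparison

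*Protocol*

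**What the plan says.** Three statements in the protocol bear on this point.

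- **Design.** Section 3.0, Objective #1, under the functional assessment heading: "A case-control approach will be used to compare patients under statin treatment with and without MRSE". The MRSE cohort numbers 60 and may be on any statin at any dosage. For the comparators, "30 patients without MRSE under statin monotherapy (paired for statin and dosage with the MRSE cohort) will be evaluated".
- **Endpoint.** The same section: "The primary efficacy parameter will be the percent change for these measurements from baseline to end of each phase of the study".
- **Tests.** Section 5.0 compares subgroups with and without symptoms on percent change. For means, "One-way ANOVA will be used to compare means of continuous variables". Proportions "will be compared using either the Chi-square test, or the Fisher's exact test when appropriate".

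The protocol nowhere describes a matched or stratified analysis of this comparison, or an adjustment for statin or dosage. It does not say whether pairing is done patient by patient or by balancing group frequencies.

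**The concern.** One-way ANOVA has a single factor, and with two groups it equals the pooled t-test. Chi-square and Fisher's exact test also treat the groups as independent samples. Pairing on statin and dosage makes the groups alike on those two variables. If the variables influence the percent change, the variation they cause is balanced out of the group difference but stays in the ANOVA error term. The standard error is then larger than the design warrants. The trial restricts its choice of comparators to obtain balance, and its analysis gives up the precision that could come with it.

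This touches one contrast only: patients with versus without MRSE.

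**Working it through.** **The plan's own figure.** Section 5.0 judges 60 MRSE patients (30 per randomised arm) sufficient. The power calculation is in an appendix that is not in the available text, and no target power or difference is visible. The figure therefore cannot be reproduced and is not used here.

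**Inputs**
- Group sizes 60 and 30, two-sided alpha 0.05 (protocol).
- Difference 22, SD 43: the extensor-strength change in the nine preliminary MRSE patients. Using it as a between-group difference assumes no mean change in patients without MRSE and the same SD. This is an assumption.
- Within-match correlation rho, meaning the correlation of percent change between patients on the same statin and dosage. The documents give none, so a range is shown.

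**Formulas, for 30 sets of two MRSE and one non-MRSE patient**
- Standard error used by the ANOVA: 43 × √(1/60 + 1/30) = 43 × √0.05 = 9.6.
- Actual standard error, since a shared set effect cancels in the difference: 9.6 × √(1 − rho), which is 9.1, 8.6 and 8.0 at rho 0.1, 0.2 and 0.3.
- True ANOVA error rate: 2 × [1 − Φ(1.96/√(1 − rho))] = 3.9%, 2.8% and 1.9%.

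**Simulation, 30 sets of 2:1, statin and dosage acting alike in both groups, 40,000 runs per cell**

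| rho | ANOVA error rate | ANOVA power | Matched power | Gain (points) |
|---|---|---|---|---|
| 0 | 5.2% | 61.8% | 61.3% | −0.5 |
| 0.1 | 3.8% | 62.6% | 66.3% | 3.6 |
| 0.2 | 2.9% | 63.6% | 71.4% | 7.8 |
| 0.3 | 2.0% | 64.3% | 77.0% | 12.7 |

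The matched analysis held 4.9% to 5.2% throughout.

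**Frequency matching.** With five statin-by-dosage strata in place of sets, power at rho 0.1, 0.2 and 0.3 was 63.1% vs 66.2%, 65.1% vs 71.9% and 66.6% vs 76.9%. The ANOVA error rates were 4.0%, 3.4% and 2.6%. The result does not depend on individual sets.

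**What each rho implies.** The SD between statin/dosage sets is 43 × √rho: 13.6 points at rho 0.1, 19.2 at 0.2, 23.6 at 0.3 and 30.4 at 0.5. From 0.3 upwards it exceeds the whole assumed effect of 22.

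**Statin and dosage acting only in MRSE patients (same 30 sets)**

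| rho | Power, ANOVA vs matched | Error rate, ANOVA vs matched |
|---|---|---|
| 0.1 | 62% vs 63% | 5.8% vs 6.1% |
| 0.2 | 62% vs 64% | 5.7% vs 6.7% |
| 0.3 | 61% vs 65% | 6.5% vs 7.9% |

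Here the gain is about 1 to 3 points (rounded entries can differ by one more), the ANOVA is no longer conservative, and the matched model lies further above 5%.

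No figure was computed for the Chi-square or Fisher comparisons. The reasoning there is qualitative.

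**The case against.** The strongest case on the other side has five parts.

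1. **The loss is conditional.** Nothing in the documents links statin or dosage to the percent change. Section 2.0 reports MRSE in 10% of patients overall and 16% for some statins, but that is symptom prevalence, not change in muscle function. This stands.
2. **A high correlation is doubtful.** Most preliminary patients were on low doses, the highest being 20 mg, and the ±15% test-retest variation of the dynamometer is noise that matched patients do not share. A reader might infer a large loss, such as 67% against 89% power at rho 0.5. The documents do not support a correlation of that size.
3. **The direction depends on similar effects in both groups.** The protocol's hypotheses place the deficit and its recovery in MRSE patients. If the statin and dosage effect lies only there, the benefit nearly vanishes. This stands.
4. **Nothing is biased.** A reader might infer that ignoring the pairing invalidates the estimate. It does not: the balance from pairing remains in the unadjusted difference.
5. **The contrast is not singled out.** A reader might take MRSE versus non-MRSE as the sole primary comparison. Section 3.0 names percent change without fixing the contrast, and section 5.0 bases the sample size on withdrawal and vitamin D effects in MRSE patients.

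It could also be said that adjustment belongs in a statistical analysis plan. That does not dispose of the point, because section 5.0 does not leave the test open. It names one that omits a factor the design was built on.

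**Conclusion.** The mismatch between the paired design and the named tests is real. Its cost is uncertain. If statin and dosage predict the percent change similarly in both groups, the ANOVA gives up about 3 to 4, 8 and 13 points of power at correlations of 0.1, 0.2 and 0.3. This assumes a between-group difference taken from nine patients' own change. At a correlation near 0 there is no loss, and if the effects lie in MRSE patients only there is little to gain.

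This is a cheap improvement in precision, not a threat to validity. The within-patient change on withdrawal and the randomised vitamin D comparison are not affected.

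**What to change.** In section 5.0, for the Objective #1 comparison of patients with and without MRSE:

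- State whether pairing is individual or by frequency.
- Replace the one-way ANOVA by a linear model with group plus statin-by-dosage stratum, pooling sparse strata. Use the matched set as the factor only if pairing is done individually. Strata have the advantage of keeping patients whose partner withdraws.
- For proportions, use a Cochran-Mantel-Haenszel test over the same strata.
- Keep the 10 statin-naive controls outside this model.

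The cost is one or two sentences and a few degrees of freedom: 7 with, say, eight strata (8 − 1), or 29 with individual sets (30 − 1). If statin and dosage prove irrelevant, the power lost is under 1 point. No new data are needed, because statin and dosage must be known to make the pairing.
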